### Statistical analysis

#### Sample size

Sample size calculation was based on the expected fraction of women assigned to regular monitoring either on the basis of the prediction rule or gestational age at the time of previous delivery (67%), the expected failure rate within this category (2%), a type I error (one-sided) of 0.05 and a type II error of 0.2. In order to be able to exclude failure rates of 5% or more, 150 patients assigned to regular monitoring are needed. This means that results of about 225 patients in the recurrence risk based care are needed. The estimated number of 250 allows for drop out and incomplete data of 25 patients.

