As the care provided to women assigned to regular monitoring is less intense, a possible consequence may be that the detection of clinical signs of preeclampsia or HELLP syndrome is somewhat later than in the current care as usual approach. However, we do not expect this to lead to adverse maternal or fetal outcomes, because the prediction model suggests that the recurrence rate in this group is low (< 1%) whereas there is also increased alertness for early signs of pregnancy complications in women with a history of preeclampsia or HELLP syndrome.

In summary, the PreCare study is designed to provide information on whether recurrence risk guided care is a worthwhile strategy compared to current care for pregnant women who suffered from preeclampsia or HELLP syndrome during their previous pregnancy.

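### 150 women in regular monitoring do not give 80% power to exclude a 5% failure rate at a true 2%; exact power is about 42%

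*Protocol article*

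**What the plan says.** The Sample size section of the protocol article gives every input to a single-group calculation: "the expected failure rate within this category (2%), a type I error (one-sided) of 0.05 and a type II error of 0.2". The rate to be ruled out is 5%, and the result is "In order to be able to exclude failure rates of 5% or more, 150 patients assigned to regular monitoring are needed". With 67% of women expected in regular monitoring, the section moves from 150 to about 225 evaluable women in risk-guided care, and then to 250 to allow for 25 with drop-out or incomplete data. It names no test and no interval method.

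The Discussion gives another figure for women assigned to regular monitoring: "the prediction model suggests that the recurrence rate in this group is low (< 1"%).

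The Abstract names recurrence in the regular monitoring group as the primary outcome. This is the only sizing calculation in the article.

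**The concern.** At a true 2%, 150 women are expected to produce 3 failures. For power of 80%, a result somewhat worse than 3 must still exclude 5%. Yet the exact one-sided 95% upper limit for 3 of 150 is 5.09%, so even the expected result fails to exclude 5%. Power therefore has to be well below 80%.

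The calculation supports the safety side of the study. The Discussion concedes that less intensive monitoring may delay detection of disease, and relies on a low failure rate in this group. If the figures are wrong, one of two things follows. Either the study will probably fail to exclude 5% even when the care performs as expected, or a lenient interval will clear a 5% failure rate more often than the stated 5% of the time.

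**Working it through.** **Inputs** (all from Sample size, except the last): true rate p1 = 0.02; rate to exclude p0 = 0.05; one-sided alpha = 0.05 (z = 1.645); power = 0.80 (z = 0.842); n = 150 in regular monitoring; 67% assigned to regular monitoring; 250 recruited. The Discussion gives a rate below 1%.

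**Steps that reproduce.** 150/0.67 = 224, stated as about 225. 225/0.9 = 250. Only the 150 is in question.

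**Attempt to reproduce 150 by normal formulas**, with difference 0.03:

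- Null and alternative variance: [(1.645·√0.0475 + 0.842·√0.0196)/0.03]² = [(0.3585 + 0.1178)/0.03]² = 252.1, so 253.
- Variance at 2% only (Wald): (1.645 + 0.842)²·0.0196/0.0009 = 134.6, so 135.
- Variance at 5% only: (1.645 + 0.842)²·0.0475/0.0009 = 326.3, so 327.
- Arcsine: 221.1, so 222.

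None gives 150. Only the Wald formula falls below it.

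**Exact binomial at n = 150**, X = number of failures:

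| Exclude 5% if X ≤ | P at 5% (type I error) | P at 2% (power) | P at 1% (power) | Exact 95% upper limit (one-sided) |
|---|---|---|---|---|
| 2 | 0.018 | 0.421 | 0.809 | 4.14% |
| 3 | 0.055 | 0.647 | 0.935 | 5.09% |
| 4 | 0.126 | 0.817 | 0.982 | 6.00% |

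- *Exact test.* The largest limit with type I error at or below 0.05 is 2 failures. Power at 2% is 42.1%, so the type II error is 0.58 rather than 0.20.
- *Score test.* At 3 failures, z = (0.05 − 0.02)/√(0.0475/150) = 1.686, above 1.645, so 3 failures are accepted. Power is 64.7% and the true type I error 5.5%. The mid-p rule gives the same limit.
- *Wald limit.* At 4 failures it is 0.0267 + 1.645·√(0.0267·0.9733/150) = 4.83%, below 5%, so 4 failures are accepted. Power is 81.7% and the true type I error 12.6%, which is 2.5 times the stated 5%.

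**Sample size that meets the stated inputs (exact).** Power first reaches 80% at n = 234 (limit 6 failures, type I error 0.0499, power 0.809). Because exact power moves in a sawtooth, it stays at or above 80% only from n = 286. At 67% assigned, 234/0.67 = 349, so about 350 evaluable women would be needed in risk-guided care, against the stated 225.

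**If nobody drops out.** 250 × 0.67 = 167.5. With n = 167 the limit is 3 failures (type I error 0.030) and power at 2% is 57.1%.

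**What 150 women can exclude.** With 4 failures allowed (power 81.7% at a true 2%), the exact upper limit is 5.998%. So 80% power exists for excluding about 6%, not 5%.

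**The case against.** The strongest defence is that the article names no method. Under a normal approximation with the variance taken at 2%, 135 women suffice, and 150 has nominal power of 83.6%. On that reading the authors' arithmetic is not wrong, only their approximation. This does not rescue the statement. With about 3 expected events the approximation is poor, and its rule has a true type I error of 12.6%, while the same sentence of the protocol fixes 5%. One could guess that 150 is 135/0.9, but the step from 225 to 250 already allows for drop-out, so that would count it twice.

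A fair second point is that 42% is a low point of the sawtooth: at n = 150 the exact rule uses only 1.8% of the 5% allowed. With 153 women the limit becomes 3 failures and power is 63%. That stands, and a range of 42% to 65% across exact and score methods describes the position well. But 63% is also the highest exact power at any size up to 180, so the shortfall does not depend on the trough.

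Third, the 2% covers women assigned either by the model or by gestational age at the previous delivery, whereas the rate below 1% is attributed to the model. The two might describe different women, or 2% might be a cautious planning value. The Discussion, however, applies its figure to the regular monitoring group without that distinction. The 81% power at a true 1% may be coincidence, and it does not show that 1% was used.

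Finally, the Data analysis section describes a comparison with usual care and states no decision rule against 5%. The 12.6% error would therefore arise only if a Wald limit were used at the analysis. The sizing statement remains wrong either way.

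**Conclusion.** The concern holds. With the protocol's own inputs, 150 women give 42% power by the exact test and 65% by the score test, against the 80% stated. With complete data on all 250 (about 167 in regular monitoring), exact power is 57%. No method examined gives both a type I error of 5% and power of 80% at n = 150: the only one that reaches 80% has a type I error of 12.6%.

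This rests on reading the calculation as a single-group comparison with a fixed 5%, which is how the section words it, and on independent outcomes between women. The result depends heavily on the true rate: exact power at n = 150 is 81% at 1% and 42% at 2%. The two expected rates in the article are therefore not interchangeable.

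**What to change.** Keep the enrolment and rewrite the sample size paragraph:

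- State that 150 women in regular monitoring give about 42% power to exclude a failure rate of 5% or more at a true 2% (exact, one-sided 5%), and about 80% power to exclude 6% or more. The 6% describes what this sample can do; whether it is an adequate limit is a separate clinical judgement that the authors must make.
- Name the interval. An exact (Clopper-Pearson) upper limit respects the stated 5%; a Wald limit does not and should be ruled out.
- State that all women in regular monitoring with an outcome are analysed, about 167 if data are complete, for 57% power.
- Reconcile the 2% in Sample size with the rate below 1% in the Discussion, saying which women each describes, and show power at both (42% at 2% and 81% at 1%, for 150 women).

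The cost is a reworded paragraph and a less favourable stated power. No extra patients are needed. If the authors instead want to keep 80% power for 5% at a true 2%, they need at least 234 women in regular monitoring, or about 350 evaluable in risk-guided care.

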#### Data analysis

The primary analysis concerns the incidence of recurrent early-onset preeclampsia or HELLP syndrome in both groups (recurrence risk guided care versus care as usual). Analyses will be adjusted for potential confounders (including demographic factors). Confidence intervals will be adjusted by means of multilevel analysis (hospital).

We will also analyse whether the new patient data indicate the need for an update of the predictive model. For this purpose, we will first compare the characteristics of the original population used for model development with the new population, the so-called "validation population". For example, the incidence of early-onset preeclampsia may differ between the original and validation population. It is also possible that the latter population has a different case-mix (i.e. differences in distributions of the predictors in the population), because, e.g., more hospitals are included. In addition, different predictor-outcome associations and additional predictors, that are not included in the model but are either more or less frequent in the new population, could play a role. We will also assess model performance in the validation population by comparing sensitivity, specificity, positive and negative predictive values and discrimination and calibration compared to the performance in the derivation population.

If the analysis should indicate lower accuracy than expected, we will analyse to what extent all these factors indeed affect the model's accuracy and update the model to obtain adequate accuracy. Updating of the model will be done by means of re-calibration (step 1) and model revision (step 2) [24-26].

#### Economic evaluation

A cost-effectiveness analysis will be performed from a societal perspective, comparing the costs and effects of recurrence risk guided care versus care as usual. The time horizon of the study is 9 months (3 mo amenorrhea - 3 mo post partum). Discounting is not relevant given the short time horizon.

The cost analysis will be performed according to the Dutch guidelines for cost calculations [27]. All hospital resource use and costs associated with care for pregnant women and their newborns will be calculated from study entry until 3 months post partum and include costs such as outpatient visits and hospital admissions. Cost prices will be obtained from participating hospitals. If prices are not readily available, directive prices will be used [27] or additional calculations will be made. Costs in the analysis also include direct non-health care costs (travel costs) and indirect costs (productivity loss).

Effect parameters are clinical outcomes, health related quality of life, anxiety, depression and posttraumatic stress.

Currently, no economic evaluation methods are available that integrate health outcomes of both mother and child into a single outcome measure. However, preeclampsia may have health effects for both the pregnant women and her (unborn) child. Therefore, the main cost-effectiveness analysis will involve calculating two incremental cost-effectiveness ratios (ICERs) expressing 1) the cost per Quality Adjusted Life Year (QALY, mother unit of analysis) and 2) the cost per live born infant (child unit of analysis). To this end, a decision model will be developed. Modelling in economic evaluation is considered useful for example when experimental observations from a trial are missing, which in this study applies to some parameters in the care as usual group [28,29].

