**Methods/design:**

We developed a prediction model to estimate the individual risk of recurrence of early-onset preeclampsia and the HELLP syndrome. In a before-after study, pregnant women with preeclampsia or HELLP syndrome in their previous pregnancy receiving care as usual (before introduction of the prediction model) will be compared with women receiving recurrence risk guided care (after introduction of the prediction model).

Eligible and pregnant women will be recruited at six university hospitals and seven large non-university tertiary referral hospitals in the Netherlands.

The primary outcome measure is the recurrence of early-onset preeclampsia or HELLP syndrome in women allocated to the regular monitoring group.

For the economic evaluation, a modelling approach will be used. Costs and effects of recurrence risk guided care with those of care as usual will be compared by means of a decision model. Two incremental cost-effectiveness ratios will be calculated: 1) cost per Quality Adjusted Life Year (mother unit of analysis) and 2) cost per live born child (child unit of analysis).

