### Data collection

For the prospective assessment (n = 50 care as usual; n = 250 recurrence risk guided care), baseline demographics, past obstetric and medical history will be recorded in case report forms. Information is obtained on the condition of mother and child, infant weight, infant length, morbidity and mortality from the infant and maternal records. If applicable, details of the admittance of the child to the neonatal intensive care, high care or medium care unit will also be collected. All activities in the hospital will be documented until three months postpartum.

We will assess not only clinical outcomes, but also health-related quality of life by using the EQ-5 D [19], anxiety by using the STAI [20], depression by using the Beck Depression Inventory [21] and posttraumatic stress by using the PTSD Symptom Scale [22]. The QoL questionnaires will be administered at 3-month intervals between baseline (before 20 weeks of pregnancy), at 29 weeks of pregnancy, ten days and three months postpartum. Costs outside the hospital, such as GP care, midwife and maternity care, productivity losses and out-of-pocket expenses will be obtained by means of a retrospective cost questionnaire with a recall period of 3 months. Long-term follow up of the women and children may be possible, but is not included in the current study.

For women enrolled in the retrospective assessment (n = 200), all data described above will be collected, except data on health-related quality of life, anxiety, depression, posttraumatic stress and costs outside the hospital.

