#### Study outcomes

Recurrence risk guided care will be compared with care as usual with respect to several outcomes.

Primary outcome is the occurrence of either early-onset preeclampsia or HELLP syndrome. Early-onset preeclampsia and early-onset HELLP syndrome are defined according to the criteria of the International Society for the Study of Hypertension in Pregnancy with the criterion of delivery before 34 weeks after the last menstrual period [23]. Secondary clinical outcome measures are: gestational age of onset of preeclampsia, eclampsia, HELLP syndrome, intrauterine growth restriction, caesarean section, admission to the neonatal intensive care unit (NICU), gestational age at delivery and maternal/infant mortality. Other secondary outcome measures are societal costs, quality of life, anxiety, depression, development of posttraumatic stress, satisfaction with treatment, protocol adherence and cost-effectiveness.

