## Discussion

This study is expected to yield information on health outcomes and costs of adjusting the level of care to the estimated probability of recurrent preeclampsia. The results can provide a basis for more uniform (and evidence-based) guidelines for care for formerly preeclamptic women and possibly lead to more cost-effective provision of health care. With respect to health care costs, it is expected that mean costs per patient will decrease as a result of a reduction in intensive maternal and fetal surveillance. Potential savings can be even higher, since the majority of women assigned to regular monitoring may be adequately served by care provided by in-hospital midwifes [30].

The close cooperation with many centres enables us to reach a representative study population of pregnant women who have experienced preeclampsia in their previous pregnancy, which enhances the applicability of the results to all former preeclamptic women. Results of this study will be disseminated by means of presentations at scientific meetings and peer-reviewed publications. Study outcomes will also be communicated directly to the NVOG (Dutch Association of Obstetrics and Gynaecology), KNOV (Royal Dutch Association of Midwives), and the Dutch HELLP syndrome foundation. In addition, we will cooperate with the NVOG in order to produce recommendations for the formulation of guidelines. The recommendations could either be integrated into the current guideline on Hypertensive Disorders in Pregnancy, or be used to develop a new guideline. The results of this study will be used to standardise the postpartum evaluation of women with a recent history of preeclampsia or HELLP syndrome. It is expected that the number of tests in the postpartum evaluation will not only be reduced, but also synchronised.

A randomised controlled trial design is usually preferred over any other design. However, for this study such a design was not considered applicable. A before-after study was chosen (instead of a fully prospective, randomised study) because of the risk of care as usual being contaminated with the regular monitoring and intensive monitoring protocols. Because current care as usual is not standardised, and blinding of the participating gynaecologists with respect to predictive factors for recurrent disease is practically unfeasible, a randomised design could reduce the contrast between study arms and thereby threaten the validity of the results.

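### The child cost-effectiveness ratio counts costs to three months post partum but reads its effect at birth, so an infant who dies after birth counts as a full success

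*Protocol article*

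**What the plan says.** The Economic evaluation section names two incremental cost-effectiveness ratios as the main analysis: cost per QALY for the mother, and "the cost per live born infant (child unit of analysis") for the child. The abstract agrees: "cost per live born child (child unit of analysis").

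The same section states "The time horizon of the study is 9 months (3 mo amenorrhea - 3 mo post partum"). Hospital resource use and costs for the women and their newborns "will be calculated from study entry until 3 months post partum". A decision model is to produce the ratios.

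Under Data collection, "Information is obtained on the condition of mother and child, infant weight, infant length, morbidity and mortality from the infant and maternal records". The 200 retrospective women have the same items collected, apart from the questionnaire measures and costs outside the hospital. Study outcomes lists "gestational age at delivery and maternal/infant mortality" among the secondary clinical outcomes, and cost-effectiveness is also secondary.

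The Discussion says "it is expected that mean costs per patient will decrease". Of possibly later detection under regular monitoring, it says "we do not expect this to lead to adverse maternal or fetal outcomes". The article gives no live-birth rate, no infant death rate and no expected saving.

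**The concern.** The numerator and denominator of the child ratio cover different periods. Costs run for three months after delivery, and the effect stops at delivery. The primary outcome is disease with delivery before 34 weeks, so death after a preterm birth is a harm that the child-level result ought to register. As defined, it cannot. A strategy with more deaths after birth but the same number of live births would look equally effective for the child, and only its costs would differ.

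A second, smaller issue concerns the ratio as a summary. If the authors' expectations are right, a saving is divided by a difference in live births close to zero. The value and sign of the ratio may then depend on one or two infants.

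**Working it through.** **1. Time periods side by side**

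| Element | Period covered | Section |
|---|---|---|
| Stated horizon | to 3 months post partum | Economic evaluation |
| Hospital costs, mother and newborn | study entry to 3 months post partum | Economic evaluation |
| Child effect in the ratio | status at birth | Economic evaluation; abstract |
| Infant mortality | collected from records | Data collection |

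**2. What the mismatch does**

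For each group let L be infants born alive, D those of them who die before three months, and S the survivors, so S = L − D. Write Δ for recurrence risk guided care minus care as usual. The planned ratio is ΔC/ΔL. An effect matched to the cost period would be ΔS = ΔL − ΔD. The planned denominator therefore omits ΔD, while ΔC contains the care of the infants counted in D.

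The planned group size is 250 (Recruitment procedures). Taking one infant per woman for simplicity, one death after birth is 1/250 = 0.4 percentage points. If live births are equal and one group has one more death after birth, ΔL = 0 but ΔS differs from zero by 0.4 points. The article gives no infant death rate, so the expected size of ΔD cannot be derived from it.

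**3. Rough stability of the denominator**

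The plan states no figure to reproduce. Let p be the proportion of pregnancies without a live birth. It is assumed here, equal in both groups. Then

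SE = √(2p(1 − p)/250), and the 95% half-width = 1.96 × SE.

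| Assumed p | SE (points) | 95% half-width (points) |
|---|---|---|
| 1% | √(2 × 0.01 × 0.99/250) = 0.89 | 1.7 |
| 2% | √(2 × 0.02 × 0.98/250) = 1.25 | 2.5 |
| 3% | √(2 × 0.03 × 0.97/250) = 1.53 | 3.0 |

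Widening the assumption to 0.5% and 5% gives half-widths of 1.2 and 3.8 points.

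The effect on the ratio can be shown with a purely illustrative saving of 500 per woman. One extra live birth gives −500/0.004 = −125,000. Equal numbers leave the ratio undefined. One fewer gives −500/(−0.004) = +125,000.

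**4. Does a survival endpoint steady the ratio?**

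No. With 1–5% assumed non-survival and equal true rates, the SE is 0.9 to 1.95 points around an expected difference of zero. The new endpoint cures the mismatch in steps 1 and 2 but not the imprecision in step 3.

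**The case against.** Infant death is not lost to the study. It is collected and is a named secondary outcome, and clinical outcomes are among the effect parameters of the economic evaluation. That is correct, but separate reporting does not repair a main ratio that gives a death after birth the same value as survival.

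Live birth also has a practical advantage: it can be established for every pregnancy in both groups. The article does not say that vital status at three months is ascertained for each infant. For the 200 retrospective women, deaths outside the participating hospitals could be missed, perhaps more often than in the prospective women. This stands as a cost of the change.

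On instability, a reader might infer that the child ratio cannot be interpreted at all. The article does not support that. It gives no live-birth rate, and women may enter at any time up to 16+6 weeks, so the loss rate is uncertain. The ratio will come from a decision model, not from a raw comparison of 250 with 250, so the half-widths above are not the model's error. Incremental cost and effect must be computed to form the ratio, and together they settle what its sign means. The full plan may already provide for joint uncertainty or net benefit, and their absence from an article is no fault.

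A reader might also suppose that, with falling costs, a negative ratio could conceal a loss of infants. It could not: with a saving, fewer live births give a positive ratio, as step 3 shows.

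**Conclusion.** The mismatch stands and follows from the text alone: costs to three months post partum, child effect at birth. It affects one of the two main ratios, and each death after birth per 250 is 0.4 points of effect left out. How many such deaths to expect is not given. The weight is moderate, because cost-effectiveness is a secondary outcome and infant mortality is reported elsewhere.

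The instability of the ratio supports only a secondary recommendation. It rests on the authors' own expectations of lower costs and no fetal harm, and on an assumed 1–3% of pregnancies without a live birth. The resulting half-width of about 1.7–3.0 points is a rough guide.

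**What to change.** - Define the child effect as infant alive at three months post partum, the end of the stated horizon, in both the abstract and the Economic evaluation section. Keep live birth as a sensitivity analysis.
- Establish vital status at three months by the same method in both groups, and report for how many infants it is unknown, separately for the prospective and retrospective women.
- Report incremental cost and incremental effect, each with its uncertainty, beside the child ratio, unless the full plan already provides this.

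The first and third changes are wording and reporting, using infant mortality data already planned. The second may need additional record checks, mainly for the 200 retrospective women. If deaths outside the participating hospitals cannot be traced equally well in both groups, the survival result should carry that caveat and be read with the live-birth analysis.
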